**Body composition assessment**													
**DXA **^**c**^													
Whole-body	●	●			●			●			●		
**Bone assessments**													
**DXA **^**d**^													
Whole-body	●	●			●			●			●		
Lumbar spine vertebrae 1-4 (AP and AP-Lateral)	●				●						●		
Total hip	●				●						●		
Forearm (1/3 distal radius)	●				●						●		
**pQCT **^**e**^													
Radius (%: 4, 66)	●				●						●		
Tibia (%: 4, 14, 38, 66)	●				●						●		
**Muscle function **^**f**^	●	●			●			●			●		
**Questionnaires**													
Family Health (FHQ)	●												
Child Health (CHQ)	●	●			●			●			●		
Child Intention (CIQ)	●	●			●			●			●		
**Baseline education **^**g**^	●	● ^**h**^			● ^**h**^			● ^**h**^			● ^**h**^		
**Interventions**													
**Lifestyle intervention**	**End of Mo**	**1**	**2**	**3**	**4**	**5**	**6**	**7**	**8**	**9**	**10**	**11**	**12**
**Intervention groups**		●	●	●	●	●			●				
**Control group **^**i**^													●

^a^ Includes: Glucose, HbA1C, insulin, calcium, CBC-profile, lipid-profile, AST/ ALT, C-reactive protein, Estradiol, LH.

^b^ Includes: Weight, height, BMI, waist circumference, blood pressure, pulse and skin pigmentation by spectrophotometer (CM-700d/600d, Konica Minolta, Ramsey, NJ, USA).

^c^ Body composition assessed by DXA to yield: total mass (g), fat mass (g), lean + BMC (g) % BF, Android/ Gynoid ratio.

^d^ DXA measures of bone to yield: bone area (cm^2^), BMC (g), BMD (g/cm^3^).

^e^ pQCT measures both bone content [i.e. cortical density (mg/cm^3^)] and geometry [i.e. cortical area (mm^2^)].

^f^ Force plate assessment: jumping (force, power), sit-to-stand (force, power) and balance.

^g^ Basic Education: Performed by a registered dietitian; a basic review of nutrition and PA guide.

^h^ A dietitian is always present to answer questions and deal with age changes if in control.

^i^ Control group receives the 6 lifestyle interventions after completion of 12 mo of study.

### Baseline

All participants arrive at the research unit fasted for 12-hours. Child assent and parent consent are obtained. Child’s weight and height are measured to confirm BMI criteria are met. All children are tested for normal blood glucose using a glucometer; those with blood glucose above ≥ 6.9 mmol/L are advised to seek subsequent medical assessment and are not enrolled in the study. Those with a normal blood glucose value (< 6.9 mmol/L) have a 9 ml blood sample taken. Parents complete a socio-demographic questionnaire and with a researcher, the child answers a series of questions from a study-specific questionnaire (*Child Intention Questionnaire* (CIQ)). All families receive a general nutrition and PA educational session by a registered dietitian. Parents are instructed how to complete a 3-day food diary; they are provided with a pre-paid envelope and asked to mail the diary once completed. The food diary will capture 3 non-consecutive days including one weekend day. At the end of the baseline visit, children choose from a ball, ball and racket or jumping rope, as a part of remuneration for their time with the dual purpose to encourage physical activity. Parents are told which group they are in and schedule their next visit.

### Follow-up visits

Children return to the clinic every 3-months for in the 12-h fasted state for blood sampling (Table 1). Parents complete a questionnaire about child’s eating behavior, physical activity level, and sun exposure. During these visits, blood tests, anthropometry, body composition, bone assessments, and muscle function tests are performed. The CIQ is also completed. A dietitian is present at all follow-up visits to ensure parents receive the same nutrition and physical activity advice throughout the study. We believe that families require continuous support and therefore having a dietitian present at all study visits helps reduce participant withdrawal, especially for the control group.

### Measurements

#### Biochemistry

Immediately after blood is drawn, plasma samples are spun for 20-minutes. Serum samples are spun after 30 min, and used to measure insulin (0.5 ml) while plasma (0.5 ml) is used for measurement of glucose, liver enzymes (ALT, AST) and lipids (LDL, HDL, total cholesterol, TG and hormones) using autoanalzyers (Beckman Access and Beckman DxC600 CA, USA) at the Montreal Children’s Hospital (MCH) clinical chemistry laboratory (certified by the provincial quality assurance program, the Laboratoire de santé publique du QC). These samples are sent for analysis to the MCH within 4-hours of blood sampling. A pediatrician reviews all biochemical data; abnormal results are addressed on an individual basis to ensure children are healthy. These biochemical outcomes are in line with the 2006 Canadian clinical practice guidelines on the management and prevention of obesity in adults and children [55].

In addition to the recommended biochemistry, we will also examine in our research unit the following in the view of bone health outcomes and satiety. Vitamin D status is examined using plasma 25(OH)D concentration, as well as osteocalcin and PTH concentrations using an autoanalyzer (Liaison, DiaSorin, Ontario, Canada). Plasma is reserved to measure 1,25-dihydroxyvitamin D (1,25(OH)_2_D) as needed using LC-MS/MS (Warnex Bioanalytical Services, Quebec, Canada). Blood samples to analyze satiety markers are prepared by adding inhibitors (20 uL AEBSF and 20 uL DPP-4) to one 2 mL tube. Satiety markers are measured at McGill University using multiplex assays and luminex technology (EMD Millipore Corporation, Billerica, MA, USA): grehlin (acylated and nonacylated), GLP-1, neuropeptide YY, adiponectin and leptin. For red blood cell analysis, methanol-H_2_O-BHT is added in equivalent volume to red blood cell volume and spun. All CV% are <5% and typically 1 to 2%. HOMA-IR is calculated as the product of the fasting insulin (IU/ml) and plasma glucose (mmol/L)/22.5 [56].

#### Anthropometry

Anthropometry is measured using standard practices: height is measured to the nearest 0.1 cm using a stadiometer (Seca 214, Hamburg, Germany) and weight is measured to the nearest 0.1 lb using a calibrated balance-beam scale (Detecto, Missouri, USA) in standardized children’s clothing (facility’s cotton shorts, T-shirt, socks). Weight is converted to kg and BMI is calculated (kg/m^2^) and Z-scores are derived using the World Health Organization’s ANTRHO software (version 3.2.2, January 2011, Switzerland, Europe). Waist circumference is measured to the nearest 0.1 cm at the umbilicus [57]. All values are expressed in absolute units with standard deviation scores using the data from the World Health Organization [58].

#### Health measures

During all visits, a registered nurse measures blood pressure using a standard sphygmomanometer (Trimline PyMaH Corp, Flemington, New Jersey, USA) and manually takes the child’s pulse. Pubertal stage is assessed by parent’s identification of physical development using the Tanner criteria [59,60]. Fasting serum concentrations of luteinizing hormone (LH) in boys, and LH and estradiol (E2) in girls is used to confirm Tanner stage.

### Body and bone assessment

#### Dual-energy X-ray absorptiometry (DXA)

DXA is used in the pediatric population to provide measurements of BMC and areal-BMD (aBMD) [61]. As per the International Society for Clinical Densitometry [61], whole body, lumbar spine vertebrae 1 to 4, total hip and forearm (non-dominant) BMC and aBMD are measured using a Hologic 4500A clinical densitometer (APEX version 13.2:3, Hologic QDR-4500A Discovery Series, Bedford, MA). For this test, children wear standardized clothing (cotton shorts, T-shirt, socks). Values are compared to the Hologic normative databases and thus expressed as absolute BMC and BMD along with Z-scores where applicable [61]. This Hologic model also measures soft tissue composition from the whole body scan, but does not distinguish subcutaneous from visceral fat depots. Information about android and gynoid regions, adipose indices (example: ratio of fat mass: height (kg/m^2^)) and lean plus BMC indices (example: [lean + BMC]/ height (kg/m^2^)) are also available and have been validated in children [62].

To complement the waist circumference measures, abdominal adiposity will be estimated using sub-region analysis of the full torso. Total body fat (kg and %) and trunk fat (kg) values are available from the DXA software. Although DXA measures of trunk fat mass reflect fatty elements in soft tissue as well as adipose tissue in subcutaneous and visceral depots, DXA-derived measures account for 80% of the variation in intra-abdominal fat as measured by computed tomography (CT) [4] and explain 79% of the variance in insulin sensitivity [63]. Values for total abdominal fat obtained using DXA are not different from CT measures [64]. Phantom scans are conducted daily to maintain quality assurance and the CV% for the phantom BMD and BMC will be calculated over the study period.

#### Peripheral quantitative computed tomography (pQCT)

To measure volumetric BMD (vBMD) as well as bone architecture, pQCT (XCT-2000; Stratec, Pforzheim, Germany) will be used [65]. This technique distinguishes the type of bone (cortical and trabecular) [66] in the non-dominant radius and tibia. Dominance will be established by asking the child which hand they write with; that side determines the dominant leg too. A 30-mm planar scout view is used to locate a standard anatomical site for the reference line at the distal end of the limb being measured. For the radius, length of the non-dominant forearm is measured as the distance between the olecranon and the styloid process forming the basis for the location of the distal and proximal slices. Single axis 2.5-mm slices (voxel size, 0.5 mm) are measured 4% and 66% proximally from the distal end of the radius. For the tibia, length of the non-dominant tibia is measured as the distance from the distance between the palpated lateral condyle and the lateral malleolus. Single slices are measured 4%, 14% 38% and 66% proximally from the distal end of the radius and tibia.

The scans are analyzed using contour mode 2 (45%) and peel mode 1 to assess total (TB) and trabecular bone (Trab) parameters at the 4% site. At the 66% site, cortical bone (Cort) is detected with separation mode 1 and a threshold of 710 mg/cm^3^. A similar method will be used for distal tibia. Normative data for adults not pediatrics exist for this model [67] and thus values will be tested for changes over time or as absolute changes. vBMD measurements are performed with a repeated-measures program that allows the starting point to be set according to previous measurements. Phantom scans are conducted daily to maintain quality assurance and the CV% for the phantom vBMD will be calculated over the study period. Data is analyzed using the manufacturer’s software package in which the outer contour of bone is defined with a threshold of 280 mg/cm^3^.

### Muscle function

At each research visit, balance and muscle strength are determined using standardized manoeuvres on a force plate (Model 9260AA, Kistler Instrument Corp., NY, USA). This force plate measures ground reaction forces, moments, and centre of pressure during balance testing using a piezoelectric 3-component force sensor in 3 planar directions. Manoeuvres include two-legged jumps, sit-to-stand exercises and a balance test. First, in 5-second increments, children are instructed to stand on the platform, bend their knees slightly and jump as high as they can with their hands freely beside them. They perform 6 repetitions. Secondly, seated with legs at a 90-degree angle and feet firmly placed on the platform, children “hug themselves” and rise out of the chair into a standing position (~4 seconds) and then sit back down in the chair back to the initial seating position for 4 seconds before repeating this exercise for 6 repetitions. To assess balance, children randomly close or open their eyes for three different sequences, 25 seconds per sequence. This exercise is repeated in random order. All data is analysed using Bioware Software (Kistler Instrument Corp.) and statistically used with DXA, pQCT, PA questionnaire and dietary data to assess for changes in muscle strength throughout the intervention.

### Demographics and home setting

At baseline only, parents complete a questionnaire that contains questions adapted from the Canadian Community Health Survey (CCHS) [68]. This questionnaire asks for parental age at birth of the index child, education, ethnicity, family income range and current employment. Neighbourhood environment is assessed by asking parents to report on proximity to outdoor and indoor recreational facilities, supermarkets and neighbourhood safety [69]. These questions are found in the study-created questionnaire titled the “Family Health Questionnaire” (FHQ).

### Parental perceptions of child obesity, intentions, nutrition knowledge and perceived behavioral control

Parents complete a set of questions about previous dieting and weight history, specifically how they perceive themselves as a child, adolescent and adult prior to birth of the participant [15]. They self-report current weight and height and report physical activity practices using the validated International Physical Activity Questionnaire [70]. Parents are also surveyed on their perceptions of their child’s weight using a visual analog scale [71]. Nutrition beliefs and practices regarding healthy snacks and milk are assessed using questions from a validated nutrition survey [72]. Parental intention and perceived behavioral control are addressed by asking parents: “*How committed are you to participating regularly in family physical activity over the next month*?” and “*If you were motivated, how confident are you that you could participate in regular family-based physical activity over the next month*?” Parents answer on a 7-point likert scale: “extremely uncommitted”; “very uncommitted”; “somewhat uncommitted”; “somewhat committed”; “committed”; “very committed” and “extremely committed” [73]. These questions form part of the FHQ.

### Daily physical activity

Parents report their child’s weekly physical activity by completing a modified Physical Activity Questionnaire – Older Children (PAQ-C) [74]. The PAQ-C is valid for 8 y old children (Canadian) and reflects the past week and captures activity in general, at school (physical education classes, recess, lunch), after school and weekends. This questionnaire does not include time and intensity and was therefore modified using the Canada Fitness Survey for children 7 y of age and older [75]. Modifications included using the duration and intensity format from the fitness survey and MET calculations. We also included “other” questions for PAQ-C to capture screen time including video gaming and surveying non-active or interactive involvement. The PAQ-C is part of our study questionnaire titled the “Child Health Questionnaire” (CHQ).

#### Validation of mPAQ-C

In view of our modified PAQ-C, 30 children (n = 10/group), are asked to complete a 7 day activity diary to serve as a mini-validation of our modified questionnaire. To reduce participate burden the 7-day diary will be voluntary at a convenient time. This validation will include a pedometer (StepCounts Co., Diabeters Inc., Deep River, ON) and accelerometer (ActiGraph GT3X, ActiGraph LLC, Fort Walton Beach, Florida). During a visit, children are shown how to wear both accelerometer and pedometer, how to conduct a 20- step test and how to reset the pedometer. Children are sent home with the pedometer, accelerometer, a pedometer log book, activity diary and a copy of the modified PAQ-C. Children wear the pedometer and accelerometer for 7 days and at night record the pedometer wear time. Each day, child and parent complete the activity diary reflecting the activity done on that day, including the intensity of activity. To validate the questionnaire, at the end of the week, parents complete the modified PAQ-C and mail all material back to the research unit.

Data analysis includes comparing pedometer log books to accelerometer readings. Activity diary, log book and accelerometer analysis is used to validate the modified PAQ-C by quantifying activity in terms of intensity (light, moderate or vigorous), type of activity and metabolic equivalents (METs).

### Dietary intake

Dietary intake is documented using 3-d food diaries. Parents complete the food diaries before each visit at baseline, 3, 6, 9 and 12 mo. These diaries reflect 2 weekdays and 1 weekend day and have been used previously in this age group [76]. Diaries are analyzed using Nutritionist Pro software (Axxya Systems, Stafford, TX), a program that uses the Canadian Nutrient File 2010. Data are analyzed according to CFG food groups, foods considered “extras”, macronutrients (carbohydrate, protein and fat), as well as micronutrients (calcium, vitamin D, sodium, potassium and iron). Differences in dietary intake are analysed throughout the study and considered as possible covariates in all statistical analyses.

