### Outcomes

The primary outcome of this study is change in BMI Z-score from baseline to 12 months. Secondary outcome measures include changes in body weight (kg), waist circumference (cm), % body fat (%), lean body mass (g), BMD (g) and bone mineral content (BMC: g), architecture of bone (radius and tibia) as well as bone strength. Changes in food intake, PA and average time spent engaging in sedentary activity (minutes/day) are also assessed. Other outcomes include changes in eating behaviour and child’s perceptions of healthy nutrition and physical activity behaviours.

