### Intervention

In line with the Transtheoretical Model [15] and the Theory of Planned Behavior [93], this study is based on similar principles of the “Obeldicks Light” framework [94]. Our intervention is based on physical activity, nutrition education and behavioral counselling. Interventions are family-centered and use motivational interviewing techniques, specifically engaging in reflective listening, sharing decision making with the child and families, and setting realistic goals with the child [95]. For example, the interventionist suggests goals to the child and as a group, all present discuss how the goals will be attained. A goal is never set unless the child agrees to the goal and can independently strategize how they can achieve the goal in a realistic manner. All members of the family are encouraged to participate in the interventions particularly those caregivers who have a direct impact on the child’s eating and activity (i.e. meal preparation, afterschool care etc.).

Intervention sessions are held at the end of each of the first 5 mo of the study, at the end of 8 mo, concluding with a debriefing session at 12 mo. Families participate in a total of 9 hours of counselling, based on 5 × 1.5 h visits at the end of months 1 through 5. The additional visit at the end of 8 months (1.5 h) is used to determine if new diet and activity intervention strategies are necessary over time as the child grows/matures and due to season. Counselling visits at the end of months 2, 5 and 8 overlap with regular study visits and are conducted after study data is collected to limit leading and bias (same day if need be to limit travel). Table 2 outlines the overall study design. All interventions have been designed by and will be carried out by a bilingual registered dietitian with experience in physical education.

**Table 2 T2:** Differences among standard (StnInt) and modified (ModInt) treatment groups

** Standard intervention**	** Modified intervention**	**Control group**
**Nutrition recommendations **^**a**^		
Food servings per day^b^[9]:	Food servings per day^b^[9]:	Food servings per day:
•Vegetables and Fruit: 5	•Vegetables and Fruit: 5	•Will be based on the Canada Food Guide for their age.
•Grain Products: 4	•Grain Products: 4	
•Milk and Alternatives: 2	•Milk and Alternatives: 4	
•Meat and Alternatives: 1	•Meat and Alternatives: 1	
**Physical activity recommendations **^**a**^		

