**Sedentary activity**		
< 2 hours screen time per day	< 2 hours screen time per day	< 2 hours screen time per day

^a^ Children are encouraged to meet these recommendations for nutrition and physical activity. These recommendations are based on Canada’s Food Guide and the Canadian Physical Activity Guide. Children in the StnInt are reminded to engage in strength training activities, but the discussions are not as in depth as ModInt group.

^b^ If a child turns 9 their recommended to consume 6 Vegetables and Fruit; 5-6 Grains; 3 Milk and alternatives; 1 Meat and alternative.

The overall focus of the intervention is to help families make healthier lifestyle choices in terms of nutrition and physical activity, and to reduce screen time and other (sedentary behaviours). Differences between StTx and ModTx intervention lie in the CFG for children aged 4–8 y for all food group servings (Table 3). The modified intervention group is instructed to consume 4 servings of milk and alternatives per day. Although both interventions will be counselled to participate in 60-minutes of activity per day, special emphasis placed on activities that are also weight-bearing for ModTx. Examples of weight-bearing activities include jumping rope, brisk walking, dancing, racket sports (i.e. tennis) and soccer. Notably, these are also aerobic activities.

**Table 3 T3:** **Intervention protocol for standard (StnInt) and modified (ModInt) treatment groups**^**a**^

**Visit 1**	**Visit 2**	**Visit 3**	** Visit 4**	** Visit 5**	** Visit 6**

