#### Nutrition intervention and nutrition evaluation

According to the randomization, the dietitian counsels children to consume either 2 servings per day or 4 servings per day of milk and alternatives. Two servings per day is the recommendation for this age group (6–8 y). The child is given a certificate to remind parents of their specific milk and alternative requirements. Parents are also provided with the extended Health Canada list of milk and alternatives to ensure they understand this food group well. At this time, the dietitian works with the parents and child to strategize ways they can meet their recommendation. Ethically, and in line with Canada’s Food Guide, children who turn 9 will be instructed to consume 3 or 4 servings of milk and alternative as the recommendations suggest, but 3 per day accepted as meeting the servings.

At every intervention, parents and children complete a 24-h recall. Using the recall, the dietitian reinforces the appropriate quantity of milk and alternatives according to their group. If they are not meeting the recommendations, time is taken to discuss measures to get back on track and to identify barriers to change. Children are evaluated on their understanding of healthy snack choices using a modified traffic light diet evaluation, a form of evaluation often used with children [97]. The original traffic light diet uses a color-coded, calorie based exchange system [98]. We used the same concepts of coloring food choices and ask children to identify “go to foods” (green), “foods that are healthy but when eaten too much become unhealthy (yellow), and “foods that should be avoided on a routine basis, or “sometimes foods” (red). If necessary, the interventionist coaches the child by repeating the description of the food classification, but does not answer for the child. The interventionist records the answers and categorized by food group, or extra-foods (salty, sugary).

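### The Dietary intake section allows diet recorded after randomisation as a covariate in every analysis, although the intervention acts on diet, and the Statistical analysis section does not restrict this

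*Protocol article*

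**What the plan says.** All references are to the protocol article.

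- **Covariate rule** (Dietary intake): "Differences in dietary intake are analysed throughout the study and considered as possible covariates in all statistical analyses".
- **Timing of the measurement** (same section): "Parents complete the food diaries before each visit at baseline, 3, 6, 9 and 12 mo". The variables derived from the diaries include food-guide groups, macronutrients, calcium and vitamin D.
- **Diet as treatment** (Intervention): "Our intervention is based on physical activity, nutrition education and behavioral counselling". The randomised contrast between the two active arms is put this way: "According to the randomization, the dietitian counsels children to consume either 2 servings per day or 4 servings per day of milk and alternatives" (Nutrition intervention and nutrition evaluation).
- **Diet as outcome** (Outcomes): "Changes in food intake, PA and average time spent engaging in sedentary activity (minutes/day) are also assessed".
- **Primary outcome** (Outcomes): "The primary outcome of this study is change in BMI Z-score from baseline to 12 months".
- **Statistical analysis**: for comparing groups, this section names two kinds of covariate, namely characteristics found to be imbalanced at baseline and, optionally, baseline milk intake. Total energy intake and milk intake appear separately, as candidate predictors in an exploratory analysis of what determines change in adiposity and bone mass.

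**The concern.** Four of the five diary time points fall after randomisation, and diet is one of the things that randomisation is meant to change. Follow-up diet therefore lies on the path from counselling to BMI Z-score, body composition and bone. If it enters a model that compares arms, two things follow.

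First, the arm coefficient becomes the effect of assignment with diet held fixed. Whatever benefit is delivered through diet is taken out of the estimate.

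Second, the protection of randomisation is lost for that comparison. Family factors that influence both what a child eats and how the child's weight changes become confounders of the adjusted arm effect, and the resulting bias can go either way.

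Because the rule extends to all analyses and gives no selection criterion, it also leaves open whether to adjust until the data have been seen.

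**Working it through.** **1. The sections side by side**

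| Question | Dietary intake | Statistical analysis |
|---|---|---|
| Which diet values? | Differences in intake; diaries at baseline, 3, 6, 9 and 12 months | Baseline milk intake as an optional covariate; energy and milk intake as exploratory predictors |
| Which analyses? | All | Baseline covariates for group comparisons; other diet variables for determinants of change |
| Is follow-up diet kept out of arm comparisons? | No | Not stated |

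The second section is narrower, but nothing in it withdraws or limits the first.

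**2. The plan's own figure**

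Inputs from Sample size calculation: difference 0.2, SD 0.3, two-sided 5%, power 80%, dropout 10%, 39 per arm.

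- n per arm = 2 × (1.960 + 0.842)² × 0.3² / 0.2² = 2 × 7.85 × 2.25 = 35.3, rounded up to 36.
- With dropout: 35.3 / 0.9 = 39.2, or 36 / 0.9 = 40. The stated 39 reproduces to within one child.
- Completers: 39 × 0.9 = 35.1, taken as 35 per arm.
- Power at 35 per arm = Φ(0.2 / (0.3 × √(2/35)) − 1.960) = Φ(2.789 − 1.960) = 79.6%.

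This treats the calculation as one pairwise comparison without multiplicity adjustment. The covariate rule plays no part in it.

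**3. What adjustment would do**

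Let arm A shift diet by a, and let the outcome equal c × A + b × diet + error. The total effect of assignment is c + ab. With diet in the model, and no unmeasured common cause of diet and outcome, the arm coefficient is c. Writing m for the share ab / (c + ab), the adjusted effect is (1 − m) × total. The documents give no value for m, so the shares below are assumptions.

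| Assumed share m | Adjusted effect, total −0.20 | Power at 35 per arm, smaller effect only | Power at 35 per arm, simulated adjusted model |
|---|---|---|---|
| 0% | −0.20 | 79.6% | not simulated |
| 10% | −0.18 | 71% | not simulated |
| 25% | −0.15 | 55% | 45% |
| 50% | −0.10 | 29% | 26% |
| 75% | −0.05 | 10% | 10% |

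The third column puts the smaller effect into the power formula of step 2. The fourth comes from 2,000 simulated trials per share, with diet shifted by an assumed 1 SD in the treated arm. The mean adjusted effects were −0.151, −0.099 and −0.049. The unadjusted estimates stayed near −0.20, with 77% to 80% power.

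The simulated power is lower, or at best equal, because arm and diet are correlated. With a 1 SD shift and equal arms, arm explains 0.25 / 1.25 = 20% of the diet variance, which multiplies the standard error of the arm effect by 1/√0.8 = 1.12 (partly offset by a smaller residual variance). The fourth column is therefore the better guide to an adjusted model, on its own assumptions.

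**4. What the table leaves out**

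It assumes no unmeasured common causes of diet and outcome; with them, the adjusted estimate could move in either direction. It also assumes diet is measured without error. A 3-day diary records usual intake imperfectly, so adjusting for it would block less of the dietary path than the table shows.

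**The case against.** The strongest reply is that the sentence is permissive, stands in a measurement section and specifies no model. The section that describes the arm comparisons names baseline covariates and places energy and milk intake in exploratory work, which is close to the split one would ask for. Grammatically, the phrase about the whole study attaches to the analysis of diet, and the sentence does not say which time point would enter which model. The reference to all analyses also covers correlation, regression and determinants analyses, where follow-up diet is a proper predictor. A final covariate list may sit in a fuller document that is not shown.

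Much of this stands. A reader might infer that the plan commits to adjusting the primary BMI Z-score model for diet at 3 to 12 months; the article does not say so. It does state a permission that includes that model on its plain wording, and no other section limits it. That is a stated rule, not a detail left for later.

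A reader might also infer that adjusting for milk intake would remove most of the difference between the modified and standard arms. It is true that "The modified intervention group is instructed to consume 4 servings of milk and alternatives per day", and that milk servings are the only numerical difference between those two columns of Table 2. But the modified arm also receives more emphasis on weight-bearing activity (text and footnote to Table 2, and Physical activity intervention), and the Background regards the contribution of milk to body weight as unsettled. The documents do not show how much of any difference would run through milk.

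Nor do they propose follow-up activity or screen time as covariates in arm comparisons. Activity appears only among the exploratory predictors, so the point is confined to diet.

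**Conclusion.** The point holds as a defect in a stated rule. Follow-up diet is a post-randomisation variable, a target of the intervention and an outcome. Using it to compare arms on BMI Z-score, body composition or bone would answer a different question from the effect of assignment. The Dietary intake section permits this, and the Statistical analysis section, though narrower, does not prevent it.

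The harm is conditional on the option being used, and its size cannot be derived from the documents. For an assumed 0% to 75% of a −0.20 effect running through diet, the adjusted effect ranges from about −0.20 to −0.05. That range rests on a linear model, no unmeasured confounding and error-free diet data. The power figures rest further on 35 completers per arm and, for the simulated column, on a 1 SD shift in diet. They illustrate the mechanism and do not predict this trial's result. Baseline diet as a covariate, and follow-up diet in the determinants analysis, are not at fault.

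**What to change.** Replace the sentence in Dietary intake with: *Only baseline dietary intake may be used as a covariate in models comparing arms; dietary intake at 3 to 12 months is analysed as an outcome, or in exploratory determinants or mediation analyses labelled as such.* The section then agrees with Statistical analysis.

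When making the change, also settle what counts as the baseline diary. Dietary intake places it before the visit, while the Baseline section has parents post it back after a visit that ends with disclosure of the group. A baseline covariate should be recorded before the family knows its allocation.

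The cost is one sentence and that clarification. The sample size is unchanged, no new data are needed, and every exploratory use of follow-up diet remains available.
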